### Therapist selection, training, and supervision

Potential therapists for the study are identified by the site PI in conjunction with the study PI. Therapists are required to have a master’s or doctoral degree in clinical or counseling psychology, social work or psychiatric nursing, or a medical degree with specialization in psychiatry. Therapists at each site are assigned to either SNT or TAU. Therapists assigned to TAU are provided with the option of obtaining training in SNT at the end of a 2-year commitment as a TAU therapist. It is expected that most therapists would be women. However, male therapists may participate based on clinic culture and staffing patterns. We will explore the potential relationship between degree, gender, years of experience, and theoretical orientation to implementation patterns and outcome.

Training in SNT includes reading the workbook [9], which describes the theory and principles of treatment, observing a videotape of a ‘gold standard’ 16-session treatment that follows the study SNT treatment manual, and completing a training case. The training case requires completing all eight sessions of skills training and at least four sessions of exposure. The case sessions are audiotaped and supervised session by session. The test case is rated for adherence by two trained adherence raters who report deviation from protocol to the supervisor. The SNT adherence manual rates adherence to core interventions as a categorical assessment (yes or no). Successful completion of a training case is defined as achieving a 75% adherence rating on a minimum of 12 sessions which include sessions from the emotion regulation, interpersonal skills, and narrative modules. If the therapist does not reach this level of adherence, the therapist completes additional mock intervention sessions with the supervisor until she meets the criteria of 75% adherence. If adherence is less than 50%, the therapist will complete a second case. SNT supervision occurs weekly at each site with both the site PI and one of the SNT trainers (Drs. [name] and [name]).

### Fidelity monitoring

SNT and TAU treatment sessions are audiotaped and sent to the coordinating site for coding. SNT sessions are coded for therapist adherence. TAU sessions are coded to characterize their elements and to assess for presence of specific interventions in SNT using an adapted version of an established coding procedure, the Hamburg Psychotherapy Process Scale (HaPPS-O) [35]. Coding of key therapeutic elements is completed for psychodynamic, cognitive behavioral and supportive therapy, mindfulness/meditation practices as well as the specific core elements of SNT. Coding of SNT and TAU will allow a comparison of the degree to which elements in TAU may overlap with those of SNT.

SNT tapes are reviewed on a weekly basis by 10 PhD students with a Masters degree in psychology and a minimum of 2 years of clinical experience with public sector patients. Training on adherence rating requires a half-day review of the adherence rating protocols followed by practice ratings of eight tapes (five SNT and three TAU). For the SNT condition, two out of three sessions (or 67% of cases) are rated. For the TAU condition, a total of three tapes per case is randomly sampled (excluding first and last session). Each tape is assessed by two raters. The PI (MC) reviews 10% of each rater’s tapes to guard against rater drift. The PI also meets quarterly (or more frequently if needed) with raters to maintain consistent quality of ratings and to resolve identified discrepancies.

### Use of technology to enhance resources and support sustainability

There is accumulating evidence that web-based technology is an efficient and effective method of supporting clinical training [36]. We will incorporate a web-based platform to (1) make standard clinical materials readily available and easily downloadable during the treatment trial itself and (2) provide a platform through which treatment materials can be managed and clinical networks across the sites can be maintained and expanded after the study is completed. Reactions to the use of the web, including perceptions of its impact on sense of professional support, self-efficacy, and work satisfaction, as well as its potential as a tool for enhancing dissemination of evidence-based treatment will be obtained through two sets of focus group interviews with clinicians; one will be conducted around the half-way mark of the trial and the other at the end of the trial.

### Data management

The data management site will provide paper case report forms (CRFs) for the collection of all data required by the study. Data will be collected at the study site on paper and entered by the project coordinator on a daily basis to computerized user-friendly electronic version of the forms with a backend process that will identify missing, illogical, out of range, and inconsistent values for each data element. The data will be reviewed for completeness, timeliness, and accuracy on a nightly basis. If any errors are detected, an automatic electronic message will flag the error for correction. Personnel from the Data Management site will be available for consultation if needed to facilitate the correction. When no further errors are detected, the data management site will ‘lock’ the study data from further modification. No personal identifying information is included in the dataset. Original data files with identifying information are double-locked (that is, kept in locked cabinets and locked rooms) at each of the clinical sites.

### Statistical analysis

#### Sample size determination

The sample size was determined based on the primary hypotheses regarding superiority of SNT compared to TAU immediately post-treatment (at week 28 post-randomization) and with respect to course of symptoms during follow up (from 28 to 36 and 48 weeks post-randomization). Reviews of the literature indicated that the pre-post effects with STN were consistently large with Cohen’s d effect size greater than 0.80 [7,8,29]. In contrast, a review of the relatively small PTSD literature that has used TAU as a comparator and the somewhat larger PTSD/SUD literature revealed that effect sizes associated with TAU ranged widely from 0.3 to 1.2 [32,33]. The sample size was determined to allow 80% power of a two-sided test with level of significance α = 0.05 to detect (a) differences immediately post treatment with respect mean CAPS of size Cohen’s d = 0.35; and (b) differences in the course of symptoms during follow up that result in a difference of size Cohen’s d = 0.8 at 6-month follow-up. The necessary sample size depends on the variation in the TAU effects between sites, the clustering due to therapist (which reduced the effective sample size by a magnitude that depended on the correlation between outcomes of participants treated by the same therapist), the clustering due to site, (which reduces the variance of the difference between treatments, akin to pairwise *t*-test being more efficient than 2-sample *t*-test) and the correlation between the three repeated observations on a patients ranging from. We project 20% dropout prior to the first treatment session and overall 30% missing post-randomization data. Considering ranges of possible values of these factors and selecting most conservative likely combination of them determined that a total n = 352 patients from a minimum of four sites would be necessary. This sample size also allows sufficient power to detect difference of 20% in the remission rates at 28 weeks and an increase of this difference during follow-up by 25%. Regarding the hypotheses concerning the secondary outcomes, the study provided sufficient power to detect effects similar to those for symptoms severity measured by CAPS as the secondary measures are continuous.

### Hypotheses testing regarding SNT as compared to TAU

The primary hypothesis of the study is that SNT will be more effective than TAU for the treatment of PTSD, as well as for frequently co-occurring problems in emotion regulation, relationships, and general functioning. All analyses will be on the intent-to-treatment (ITT) sample with imputation for missing data. The intent-to-treat sample is defined as all randomized participants who attend at least the first therapy session at which they are notified about their treatment assignment. Testing of all hypotheses (including those concerning differences at a particular time point), will be based on models for longitudinal data [37]. Continuous outcomes such as severity of PTSD symptoms, emotion regulation problems, and interpersonal problems will be modeled with linear mixed effects model (MEM), while dichotomous outcomes, such as PTSD remission, will be modeled using generalized linear mixed effects model (GMEM).

Given the small number of sites, the ability to estimate the site variability with sufficient precision is limited. For this reason, the site and site-by-treatment and site-by-treatment-by-time interaction effects will be modeled as fixed effects and the variation between sites will be examined informally. The main effect of site will be included in all models whether or not it is significant. In order to protect against erroneous omission of important site effects, the statistical significance of the interactions involving site and treatment will be judged at level α = 0.15, and the site-specific treatment effects will be estimated with 95% CIs, rather than considered nil when not reaching statistical significance at α = 0.05 level.

### Exploratory analyses regarding SNT patterns of implementation

One aim of the study highly relevant to the concerns of implementation research, *per se*, is our plan to assess the potential benefits and/or drawbacks of allowing flexible delivery of the protocol. Flexible implementation variables will follow those used in Levitt et al. [29] and will include: number of sessions (ranging from 16 to 24), different types of flexible adaptations (repetitions, skips of key interventions) for the treatment in its entirety, as well as the number of sessions and occurrence of each type of adaptation within each intervention component (emotion regulation skills, interpersonal skills, and narrative work).

Each participant in the SNT condition will have values for these variables defining how the treatment was implemented for her. We plan to identify patterns of implementation associated with patient outcomes for patients at different levels of baseline severity. We will categorize patients according to level of baseline severity defined in various ways (PTSD severity, GAF score, number of co-morbidities). For each of these categorization schemes, patterns of implementation associated with outcome will be identified: excellent outcome (those achieving remission), good outcome (improvement but not remission), and poor outcome (no change or worsening). In addition to traditional regression models, recursive partitioning methods [38,39] will be utilized, allowing the identification of implementation patterns (groupings of implementation variables) as they are associated with baseline severity and outcome, and leading to the identification of optimal implementation patterns for given baseline characteristics.

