This article provides a description of the study design and reasons for design decisions such the selection of TAU as a comparator and the use of flexible delivery of SNT. These choices were intended to increase clinical realism and the generalizability of findings. However, they also added to the complexity of the study. The selection of TAU, which in a multisite study differs from site to site, requires consideration about how to characterize and assess TAU interventions and analytic techniques that take between-site variability in TAU into account. Similarly, the use of a flexible delivery of the test treatment incorporates clinician judgment and supports patient-centered care, but requires careful consideration about how to define and ensure adherence to the protocol. The study description below provides an example of the issues encountered in hybrid efficacy-effectiveness clinical trials. We present the rationale for our decisions and the scientific literature that guided them.

The study has two aims: (1) to evaluate the effectiveness of SNT relative to TAU primarily in regards to PTSD symptom reduction and secondarily in regards to treatment attendance, attrition, and therapist and patient satisfaction, and (2) to explore the relationship between variations in SNT treatment implementation and outcome relative to baseline severity of illness (for example, PTSD severity, GAF score). In addition, the study will obtain qualitative data concerning therapist and staff attitudes about contextual variables (for example, administrative support, clinic resources) including the use of technology (SNT resource website) that facilitate or impede implementation of the EBT and will explore their relationship to intervention delivery and outcome. These data will be collected via interviews conducted at the midpoint and endpoint of the clinical trial.

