### Randomization

Eligible participants are randomly assigned to either SNT or TAU. The study manager located at the coordinating site provides each clinical site with the treatment assignment upon a phone or text request by the project coordinator. Participants are randomized to STAIR Narrative Therapy or TAU in blocks of random size (2, 4, or 6) stratified by site. The randomization lists were generated by ‘R’, an open source statistical program. The treatment condition to which the participant is randomized is not revealed until she arrives at her first treatment session. Thus attrition that occurs between acceptance for treatment and the first session cannot be attributed to treatment assignment. The interval between completion of baseline assessment and first treatment session is expected to be no more than 2 weeks. If circumstances occur such that attendance at first session occurs more than 4 weeks after completion of assessment, the CAPS is re-administered. The outcome assessors are located at the coordinating site and are blind to the participants’ treatment condition. Unblinding concerning treatment allocation is permissible if a study participant experiences a serious adverse event and reporting to the Data Monitoring Committee (DMC) and the funder (NIMH) is required.

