## Discussion

This study is designed to evaluate the implementation of an evidence-based treatment for PTSD in public sector community settings with community clinicians. To date, there have been no large-scale clinical trials of an evidence-based PTSD treatment in the general community. While PTSD clinical trials have been completed in the VA service system, its specific veteran population as well as the policies, structures, and processes that guide implementation efforts in the VA may not generalize to public sector community mental health settings. This study, with its large sample and multi-site design is expected to yield evidence regarding the effectiveness of SNT relative to usual care on PTSD and range of comorbidities, as well as secondary outcomes such as health status and health service utilization in a chronically traumatized and impoverished patient population.

The study will also contribute to knowledge in implementation science. Specifically, the study will test a flexible implementation strategy of the study treatment, in which the therapist and the patient pair will select a subset of interventions within the three core intervention modules (emotion management, interpersonal/social skills, and narrative therapy) based on the patients’ needs and preferences. The study therefore emphasizes a patient-centered approach to the delivery of an evidence-based treatment and may be the first to provide data regarding the outcomes of treatment as they relate to specific patterns of intervention use. The sample size, along with appropriate use of state-of-the-art statistical techniques, will allow us to identify patterns of implementation (variations in selected interventions) associated with both good and bad outcomes, and in particular, as they relate to different levels of severity in psychiatric illness.

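### Aim 2 groups baseline severity and outcome into categories without a stated reason; full scales would serve this exploratory analysis better, and the power lost depends on assumptions that the plan does not give

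*Protocol article*

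**What the plan says.** The Background section of the protocol article gives the second aim as "to explore the relationship between variations in SNT treatment implementation and outcome relative to baseline severity of illness". The section on exploratory analyses of SNT implementation patterns sets out the method. Only women in the SNT arm have implementation values. On severity it says "We will categorize patients according to level of baseline severity defined in various ways (PTSD severity, GAF score, number of co-morbidities"). For each of these three schemes, implementation patterns are related to three outcome classes: "excellent outcome (those achieving remission), good outcome (improvement but not remission), and poor outcome (no change or worsening"). The tools are regression models and recursive partitioning.

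The Assessment section defines remission as loss of the PTSD diagnosis together with a CAPS of 20 or below. The Participants section requires a CAPS of at least 40 at entry. The section on SNT versus TAU hypotheses models PTSD severity as a continuous outcome.

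For Aim 2 the article states no number of severity levels, no cut-points, no interaction test, no effect size and no power.

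**The concern.** CAPS and GAF are scores and the number of co-morbidities is a count. Aim 2 asks how the link between implementation and outcome varies with severity. That is an interaction question, put to one arm only. Grouping both severity and outcome discards information where there is least to spare. Regression accepts full-scale inputs, and a tree finds its own severity cut-points.

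There is also a problem of interpretation. The top outcome class has a fixed CAPS ceiling, so a woman with a high entry score must improve further to reach it. When severity is defined by PTSD severity, a pattern that seems to mark excellent outcome at one level may partly reflect entry score.

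The aim is exploratory, but the Discussion says that the sample size, with suitable techniques, "will allow us to identify patterns of implementation (variations in selected interventions) associated with both good and bad outcomes", in particular in relation to severity. The analysis behind that expectation should use the data fully.

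**Working it through.** **1. Is there a figure in the plan to reproduce?** Not for Aim 2. The Sample size determination section covers only SNT versus TAU: "80% power of a two-sided test with level of significance α = 0.05" for "differences immediately post treatment with respect mean CAPS of size Cohen’s d = 0.35", leading to "a total n = 352 patients from a minimum of four sites would be necessary". For orientation, n per arm = 2(1.960 + 0.842)²/0.35² ≈ 128.2, rounded up to 129, or 258 in total. Allowing for 20% loss gives 258/0.8 = 323, and for 30% loss 258/0.7 = 369. The total of 352 lies between these. The therapist and site variation used are not stated, so 352 can be neither confirmed nor refuted. It is used here only to count women.

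**2. Women available for Aim 2.** The Randomization section says "Participants are randomized to STAIR Narrative Therapy or TAU in blocks of random size (2, 4, or 6) stratified by site". Assuming 1:1 allocation, SNT has 352/2 = 176. The Sample size determination section projects 20% dropout before the first session and 30% missing data overall.
- 176 × 0.8 = 141 attend a first session.
- 176 × 0.7 = 123 have data, if missing values are not imputed.

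**3. How coarse is the middle class?** Suppose improvement is read on CAPS, which the article does not state. A fall from 90 to 25 (65 points) and a fall from 90 to 75 (15 points) are then both good, because neither reaches 20.

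**4. Dependence on entry score.** On the CAPS part of the remission rule, a woman entering at 40 needs a fall of at least 40 − 20 = 20 points. A woman entering at 90 needs at least 90 − 20 = 70.

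**5. Sparse cells.** If 15% have a poor outcome (assumed), that is 0.15 × 123 ≈ 18 to 0.15 × 141 ≈ 21 women. Over three severity levels (assumed) this is 6 or 7 per level.

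**6. Power, by simulation under stated assumptions.** Severity s and implementation x are standard normal. The outcome is linear: y = r·x + r·x·s + error, with total variance near 1. The s·x term is tested at two-sided 0.05. Excellent/poor shares are 30/15, 20/15 or 40/20%.

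At n = 123, r = 0.25 and shares of 30/15%:

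| Analysis | Power |
|---|---|
| Severity and outcome both on full scale | 80% |
| Severity in unordered tertiles, outcome full scale | 60% |
| Severity in unordered tertiles, outcome in three scored classes | 45% |

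The loss from cutting both is 80 − 45 = 35 points here. It is 22 to 39 points over 18 scenarios (n = 123 or 141; r = 0.20, 0.25 or 0.30; the three sets of shares).

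A second set-up chose the interaction to give a target power for the uncut analysis. It cut severity at the median or tertiles and used a proportional-odds test on three ordered classes:

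| Target power, uncut | Loss with both cut (points) |
|---|---|
| 90% | 28–33 |
| 80% (simulated 72–81%) | 28–38 |
| 50% | 20–23 |
| 30% | 10–12 |

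Null rejection rates were 3–6% in the first set-up and about 4–7% in the second.

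**7. Where the loss is smaller.**
- Interaction of 0.10: 20–22% against 11–12%, about 10 points. At 0.05 it is about 3 points.
- The same tertiles scored as ordered (r = 0.25, n = 123): the loss falls from about 34 to 22 points.
- True effect only above an upper-tertile threshold: 59% against 48%, or 67% against 55%, so 11 to 12 points in these examples and 6 to 12 overall. Cutting severity alone then gains 1 to 5 points, provided the cut matches the threshold.

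**The case against.** Aim 2 is headed exploratory and sets no alpha, test or power target. Grouping has a visible purpose, since clinicians can use findings stated by severity level and remission status. The article does not say that only the categories enter the models, and such detail may sit in a fuller document. Remission is not a pure cut of CAPS, because it also requires loss of diagnosis, and the two lower classes are not tied to CAPS by name. The figure of 123 sets aside the stated plan to impute missing data. The simulations use one normally distributed implementation variable and quantile classes, not the plan's own variables and classes.

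All of this stands, and it limits the claim. A reader might infer that the plan forfeits 20 to 40 points of power as a fixed property, or that a powered analysis is wrong. The article supports neither reading: it gives no Aim 2 effect size, number of levels or test, and its power statement concerns SNT versus TAU only. A reader might also infer that full-scale inputs are ruled out. They are not, but the categories are the only form the text describes, and it gives no reason for them.

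**Conclusion.** The point holds as an efficiency and interpretation weakness in an exploratory aim. Two parts need no simulation: the cuts are unnecessary for the named methods, and the remission class depends on entry score, so outcome class is partly tied to severity level. How coarse the middle class is depends on how improvement is defined, which the article leaves open.

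The power loss is conditional. Under a linear interaction, cutting both inputs costs roughly 20 to 40 points if the uncut analysis would have about 50 to 90% power, and about 10 points if it would have 20 to 30%. It is less if tertiles are scored as ordered or the true effect is a threshold. These figures rest on assumed effects, class shares, cut-points and 1:1 allocation. No primary conclusion changes.

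**What to change.** In the section on exploratory analyses of SNT implementation patterns, state that:
- the Aim 2 regressions and a regression-type tree use week-28 CAPS on its full scale, adjusted for baseline CAPS;
- baseline CAPS and GAF enter as continuous predictors and number of co-morbidities as a count, with implementation-by-severity terms and a check for non-linearity;
- the severity levels and the excellent, good and poor classes are kept for descriptive display only.

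This is a change of wording and needs no new data, participants or procedures. The costs are the checks of functional form and results expressed as slopes and interactions, which are harder to read in a clinic; the descriptive display covers that. The change does not resolve multiplicity, since three severity measures are still examined against many implementation variables.

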The proposed study utilizes a hybrid efficacy/effectiveness design [10]. This type of trial focuses on the evaluation of the benefit of a treatment when applied in a community service setting under research sampling and assessment conditions. Its design has features that maintain internal and construct validity, while the treatment is evaluated under ‘real world’ clinical conditions that enhance external validity and generalizability. Generalizability features include engagement of sites with ethnically and racially diverse populations, few inclusion and exclusion participant criteria, use of community clinicians, a flexible approach to treatment application, and clinical training and supervision consistent with service environments. Aspects of efficacy designs that are maintained in the proposed study are: random assignment of patients into STAIR Narrative Therapy (SNT) or Treatment as Usual (TAU), use of reliable and standardized diagnosis assessment measures, and use of a manual to guide the protocol treatment and relatively intensive quality assurance of diagnostic assessments and of adherence to the treatment protocol.

The study also incorporates several elements of implementation science research. Clinicians are encouraged to use the SNT protocol in a flexible manner within clear limits, according to the symptoms, needs, and preferences of the specific patient. We view the incorporation of clinician-driven decisions regarding application of the protocol as an important ingredient in facilitating the use and dissemination of EBTs in the community. We will conduct exploratory analyses identifying implementation patterns and their relationship to outcomes for patients and also examine the influence of therapist and organizational characteristics likely to impact implementation. These include, but are not limited to, therapists’ attitudes about the intervention and administrative support for implementation of the intervention within the service. The study also introduces web-based technology as a resource intended to strengthen clinical networks and maintain use of study materials about which we will obtain qualitative data from clinicians regarding its perceived value.

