At the beginning of every therapy session, a five-item empirically validated suicide checklist, the Suicide Behavior Monitoring Form (SBMF) [27], is completed by the therapist. At the end of every other session (2, 4, 6, 8, and so on) study participants complete a brief (5-minute) assessment of PTSD symptoms (PCL-5) and the TSI dissociation subscale to track change in symptoms over the course of treatment. Treatment process is assessed using the Working Alliance Inventory-12 item (WAI-12) [28]. Satisfaction with the treatment and its perceived usefulness as well as satisfaction with the clinical environment (warmth, organization) is assessed using a measure developed for this study and is completed at the end of every treatment by participants as well as therapists for each treatment case.

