SNT is flexibly applied following the guidelines established in a previous study that evaluated the effects of flexible delivery of the treatment [29]. The study found outcomes to be equivalent to those obtained in a previous trial that required strict adherence to the protocol [7]. In the current study, treatment can range from 16 to 24 sessions. The type and number of sessions are determined by the clinician, whose decisions are guided by the needs of the individual patient. The study protocol allows (a) skipping protocol sessions, (b) repeating sessions, and (c) having non-protocol sessions. There are constraints, such that each of the three components of the treatment has a minimum number of sessions as follows: (1) three sessions of skills training in emotion regulation; (2) four sessions of skills training in interpersonal effectiveness; (3) five sessions of narrative work; and (4) two sessions that bookend the treatment, namely the introduction to treatment and termination sessions. This formula requires that a total of 14 sessions are committed to a particular set of interventions. The clinician can adhere very closely to the minimum requirements and use only two additional sessions to deviate from the protocol (for a total of 16) or can deviate rather substantially with the addition of 10 sessions (for a total of 24). Additional sessions may include more emotion regulation, interpersonal, narrative, or non-protocol sessions, as determined by the clinician.

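### Relating clinician-chosen session counts, repeats and skips to outcome within baseline-severity groups cannot identify 'optimal' implementation patterns; confounding by the course of treatment remains and can act in either direction

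*Protocol article*

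**What the plan says.** The section on exploratory analyses of SNT implementation takes as explanatory variables the "number of sessions (ranging from 16 to 24" and "different types of flexible adaptations (repetitions, skips of key interventions) for the treatment in its entirety", with the same quantities within each treatment component. It states that every SNT participant will have values for them. Patients are grouped by baseline severity (PTSD severity, GAF or number of co-morbidities). Patterns are then linked to excellent, good or poor outcome by regression and recursive partitioning, "leading to the identification of optimal implementation patterns for given baseline characteristics".

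On how these variables arise, the Treatment section says: "The type and number of sessions are determined by the clinician, whose decisions are guided by the needs of the individual patient". It adds: "The study protocol allows (a) skipping protocol sessions, (b) repeating sessions, and (c) having non-protocol sessions". The Background describes flexible use "according to the symptoms, needs, and preferences of the specific patient". The Discontinuation section lists reasons for stopping treatment early, including missed sessions and clinical crisis.

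The Assessment section has participants complete the PCL-5 and a dissociation subscale after every other session, "to track change in symptoms over the course of treatment". The implementation section gives these scores no role. The Discussion says the sample size and methods "will allow us to identify patterns of implementation (variations in selected interventions) associated with both good and bad outcomes".

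**The concern.** Session count, repeats and skips are not randomized and are not fixed at baseline. They accumulate while the clinician watches the patient. A patient who remains symptomatic may be given more sessions and may also end with a worse score. A patient in crisis may stop early and also end with a worse score. Both routes tie delivery to outcome through the course of treatment, which baseline severity does not capture. Recursive partitioning searches for associations and inherits the same bias.

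To call a pattern optimal for given baseline characteristics is to say which pattern should be used, and that is a causal claim. The analysis as described could present the delivery that easy responders happened to receive, or the delivery that crisis-free patients happened to complete, as the best one. This is one of the trial's two stated aims. The exploratory label lowers the strength of evidence claimed, but it does not remove bias, and neither would more patients.

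**Working it through.** The document gives no figure for this analysis, so there is none to reproduce. The check asks what a baseline-adjusted analysis shows when extra sessions truly do nothing.

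**Inputs from the document.** Total 352, so 352 / 2 = 176 in SNT (equal allocation assumed). With 20% lost before the first session, 176 × 0.8 ≈ 141. With 30% missing data, 176 × 0.7 ≈ 123. Sessions run from 16 to 24.

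**Assumed model.** Baseline severity B and mid-treatment residual severity P are independent standard normal variables.
- Tendency to more sessions: L = 0.2B + ρP + noise, with variance 1.
- Sessions: S = 20 + 2.5L, rounded and held within 16 to 24.
- Outcome (higher is worse): Y = 0.4B + 0.6P + noise, with variance 1 and no term in S.

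Y is regressed on S and B, and the slope is multiplied by 24 − 16 = 8. There are 1,500 data sets per setting.

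**Approximation by hand.** Given B, the covariance of L and Y is 0.6ρ, and the variance of L is 1 − 0.04 = 0.96. Eight sessions are 8 / 2.5 = 3.2 units of L. The spurious difference is about 3.2 × 0.6ρ / 0.96 = 2.0ρ, or 0.40, 0.60 and 0.80 SD at ρ = 0.2, 0.3 and 0.4.

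**Simulation, n = 123, true effect zero.**

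| ρ | 24 v 16 sessions (SD worse) | Longer 'significantly worse' |
|---|---|---|
| 0 | 0.01 | 2.8% (nominal 2.5%) |
| 0.1 | 0.21 | 10.9% |
| 0.2 | 0.43 | 30.1% |
| 0.3 | 0.63 | 57.5% |
| 0.4 | 0.84 | 81.7% |
| 0.5 | 1.07 | 96.5% |

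With n = 141 the results are similar (64.3% at ρ = 0.3). At ρ = 0.3 and n = 123, remission is 41% with 18 sessions or fewer and 19% with 22 or more (33% and 27% at ρ = 0). The best single split on sessions favours shorter treatment in all three baseline-severity thirds in 56% of data sets, against 15% at ρ = 0. If each extra session truly helped by 0.03 SD (8 × 0.03 = 0.24 SD better), the baseline-adjusted analysis would still show longer treatment 0.41 SD worse.

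A second set of assumed coefficients, n = 141, gives 0.33, 0.69 and 1.13 SD at correlations 0.2, 0.4 and 0.6, significant in 22%, 72% and 98%.

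**Adding early stoppers** (n = 141, correlation 0.4, true effect zero, a similar model):
- No stoppers: 0.65 SD worse, significant in about 69%.
- 20% stopping at random before session 14: 0.07 SD worse, 11%.
- 20% stopping in relation to poor progress (0.5): 0.12 SD better, 'significantly better' in 24% and 'significantly worse' in 0%.

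**Using mid-treatment severity.** Adding P without measurement error, in the first model, brings the difference to about 0.00 SD with 4.3% to 5.5% rejection. With a PCL-5 of assumed reliability about 0.85, in the second set, the differences become 0.08, 0.18 and 0.33 SD, significant in 6%, 11% and 27%. A landmark version at correlation 0.4 goes from 0.66 SD and 72% to about 0.15 SD and 10%.

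**How adjustment can go wrong.** Where delivery helps only by lowering mid-treatment severity, ordinary adjustment for that severity turned a true benefit of 0.24 into about 0. PCL-5 measured after an adaptation should therefore not be entered as a plain covariate.

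**The case against.** The strongest reply is that the text is mostly modest. The section is headed exploratory, the aim is to explore a relationship, and most sentences speak of association, including the Discussion sentence quoted above. The word 'optimal' stands nearly alone. That is fair, and it makes the wording change small. But it is the stated end product of the analysis, and the section gives no caution about selection by clinicians.

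Second, the article uses baseline severity to group patients and lists no regression covariates. A reader might infer that on-treatment scores are excluded, but silence does not show that, and a fuller plan may use them. What stands is that the conclusion is framed as conditional on baseline characteristics alone.

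Third, the documents speak of needs, symptoms and preferences, not of progress, and do not say that clinicians see the PCL-5. That choices respond to progress is an inference, though a strong one, because skipping, repeating and adding sessions happen during therapy.

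Fourth, a reader might infer from the 16 to 24 range that early stoppers are left out. The documents do not support this: all analyses are said to use everyone who attended a first session, and each SNT participant is to have values. The range is the permitted length of treatment. It does not cover those who stop early, so the passages need reconciling, but that is not evidence of exclusion.

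**Conclusion.** The point holds as a mismatch between method and conclusion: conditioning on baseline severity cannot turn non-randomized choices made during treatment into optimal patterns. It deserves a change but is moderate in weight, since it concerns an exploratory second aim and leaves the SNT versus TAU comparison untouched.

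A reader might infer that the analysis will make longer treatment look harmful. That is only one possible direction. It appears among patients with at least 16 sessions, at roughly 0.3 to 1 SD for correlations of 0.2 to 0.6, and it nearly vanishes or reverses once 20% early stoppers are included. All sizes rest on assumed coefficients, and the regressions use a continuous outcome, not the planned three categories. The mechanism is shown; the sign and size in this trial are unknown.

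**What to change.** 1. Replace the claim of optimal implementation patterns with patterns associated with outcome.
2. Use the alternate-session PCL-5 scores in a landmark analysis: fix a session, take those still in treatment, and relate delivery after that session to outcome, adjusting for baseline and for PCL-5 up to that session. A marginal structural model or another g-method is an alternative. Do not adjust by ordinary regression for PCL-5 measured after the adaptation.
3. Reconcile the 16 to 24 range with the statement that each SNT participant has values, and report those who stop early as a separate category.

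The cost is wording and some extra exploratory analysis of data already collected. The landmark set will be smaller than the full SNT arm. Some confounding will remain, because the PCL-5 is self-reported and imperfectly reliable.
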